## Abstract

**Background:**

Women experience changes both physically and psychologically during their transition to motherhood. The postnatal period is a critical time for women to develop maternal self-efficacy. Mobile health interventions may offer a way to reach women during this critical period to offer support and information. Essential Coaching for Every Mother is a text message program that seeks to educate and support women during the first 6 weeks postpartum.

**Objective:**

The primary effectiveness objective is to compare the effectiveness of the Essential Coaching for Every Mother program on maternal psychosocial outcomes (self-efficacy, social support, postpartum depression, and postpartum anxiety) immediately after the intervention and 6 months postpartum, collectively as well as stratified by parity. The primary implementation objective is to evaluate the implementation extent and quality of the Essential Coaching for Every Mother program.

**Methods:**

This will be a hybrid type 1 effectiveness-implementation randomized controlled trial. A total of 140 mothers-to-be or new mothers from Nova Scotia will be recruited and randomized to the intervention or control arm, stratified by parity. The intervention arm will receive the Essential Coaching for Every Mother program, which consists of 53 messages sent twice a day for the first 2 weeks and daily for weeks 3 through 6. The control group will receive usual care. Messages are personalized based on the infant’s age and the woman’s self-selected preference for breastfeeding or formula feeding and tailored with the infant’s name and gender. Women can enroll in the program if they are ≥37 weeks pregnant or within 10 days postpartum, with the first message designed to be sent on the second evening after birth. The actual number of messages received will vary based on the timing of enrollment and the infant’s date of birth. Participants will complete questionnaires assessing self-efficacy, social support, and postpartum depression and anxiety at baseline (enrollment after birth) and 6 weeks (postintervention) and 6 months postpartum. Implementation data will be collected throughout the trial, and evaluation feedback will be collected at 6 weeks from women who received the intervention.

**Results:**

Recruitment for this study started on January 5, 2021, and is currently ongoing, with an anticipated date of recruitment completion of January 2022.

**Conclusions:**

This study will assess the effectiveness of a postpartum text message program to improve maternal self-efficacy and social support while decreasing postpartum depression and anxiety. It will also shed light on the implementation effectiveness of the program.

**Trial Registration:**

ClinicalTrials.gov NCT04730570; https://clinicaltrials.gov/ct2/show/NCT04730570

**International Registered Report Identifier (IRRID):**

DERR1-10.2196/27138

## Introduction

### Background

During the postpartum period, women require support and information to ensure a smooth transition and adjustment to motherhood, which is reflected in both the World Health Organization’s postnatal guidelines [1] and the Public Health Agency of Canada’s maternity and postnatal care guidelines [2]. Worldwide, the postnatal period is often neglected in the provision of quality care [1,3]. During pregnancy, women are regularly monitored, especially during the third trimester with weekly or biweekly appointments, yet after they give birth the frequency of monitoring is significantly reduced to only once or twice in the first year, typically first around 6 weeks postpartum [4,5]. The amount and type of postpartum care that women receive for themselves and their infants depend on whether they are being followed by doctors or midwives, they are considered to have high needs, or they have identified health concerns for themselves or their infants [6].

Although the postnatal period provides an opportunity to educate and support new mothers, many women have reported not having enough information to help them in their transition to motherhood, resulting in challenges to their psychosocial adjustment [7,8]. While the postpartum period may be uncomplicated for some women, evidence suggests that others may struggle with low self-efficacy [9], feel isolated or struggle with low social support [9,10], and experience symptoms of anxiety and depression [10,11]. There is a need to develop and evaluate innovative approaches to educate and support women during this period to ensure that maternal psychosocial health needs are met and concerns are addressed in a timely manner. Evidence suggests that women are turning to online and mobile apps for sources of information during the perinatal period [12,13]. Therefore, there is an opportunity to develop a standardized, evidence-based mobile health (mHealth) intervention to address known concerns around maternal psychosocial adjustment to enhance their feelings of self-efficacy and social support while decreasing levels of postpartum anxiety and depression.

While postpartum mobile apps are also growing in prevalence, a recent systematic review identified 48 mobile apps of varying quality [14]. Also, mobile apps require access to data plans, rely on push notifications that may not be enabled, and are time consuming to build. On the other hand, one aspect of mHealth that shows significant promise is text messaging because of its cost-effectiveness, broad reach, and simplicity of use. There is some evidence that text messaging programs can enhance maternal and newborn outcomes and engage mothers during the postnatal period [15,16]. Existing postpartum text message programs focus on various postpartum topics—text4baby aims to improve perinatal health for women and their infants [17], MobileMums is focused on enhancing physical activity [18], and MumBubConnect’s goal is to promote breastfeeding [19]—yet no postpartum text message programs are currently available in Canada. The provision of timely health information can influence behaviors through repeated and relevant health messages [20]. Text messages can be sent, saved, and retrieved at any time [21], are able to be personalized and tailored, and can be provided through one- or two-way communication [22]. Therefore, a text message program was designed with low barriers to entry, low cost for participation, and ease of development and modification.

Our team developed Essential Coaching for Every Mother, an evidence-based postpartum text message program, with the goal of improving mothers’ access to information about caring for themselves and their newborn during the immediate 6-week period after birth [23]. The program was developed through iterative testing with mothers and postpartum health care providers [23] and showed preliminary effectiveness and uptake during a pilot pre-post intervention study offered during COVID-19 [24].

### Effectiveness Objectives

The primary effectiveness objective of this study is to compare the effectiveness of the Essential Coaching for Every Mother program to standard care on self-efficacy measured immediately after the intervention. The secondary objectives are (1) to compare the effectiveness of the Essential Coaching for Every Mother program to standard care on social support, postpartum anxiety, and postpartum depression immediately after the intervention; (2) to determine whether the effect on any outcomes differs based on parity (multiparous or primiparous); and (3) to compare any long-term impacts of the Essential Coaching for Every Mother program on the above outcomes at 6 months postpartum.

### Effectiveness Hypotheses

The primary hypothesis is that the Essential Coaching for Every Mother program will result in higher self-efficacy for participants who receive the intervention compared with standard care. The secondary hypotheses are that (1) Essential Coaching for Every Mother will result in higher levels of social support, lower levels of postpartum anxiety, and lower levels of postpartum depression for those who receive the intervention compared with standard care; (2) there will be no difference based on parity on any of the psychosocial outcomes; and (3) changes in psychosocial outcomes will be maintained over time.

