### Sample Size

The sample size was calculated based on the primary outcome of self-efficacy using the findings from our feasibility study [24], which showed a mean difference in self-efficacy scores between baseline and 6-week follow-up of 3.78 (SD 4.5). Therefore, with stratification by parity and a moderate intraclass correlation of ρ=0.2, a sample size of 30 participants per cluster and 60 participants per group (120 total participants) is required to be powered for analysis at the level of parity. In the feasibility study, there was an incompletion rate of 15.5%; thus, the estimated sample size will be increased by 15% to 69 participants per group, rounded up to 70 participants. In total, 140 participants will be enrolled in the study.

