### Data Analysis

Data will be analyzed on an intention-to-treat basis (excluding women who requested to stop receiving the messages or were lost to follow-up). Demographic characteristics on maternal age, marital status, education level, and delivery method will be expressed as means and standard deviations or percentages, as applicable, based on group allocation. Postnatal contacts for themselves and their infants, health concerns, and feeding behavior will also be expressed as means and standard deviations or percentages, as applicable, based on group allocation. Any significant differences in baseline characteristics, examined through a chi-square analysis or Mann-Whitney test, will be adjusted for in the analysis. A *P* value of 0.05 will be considered significant for all outcomes.

For the primary outcome of self-efficacy, a total score will be reported using means, standard deviations, and percentages. Analysis of covariance (ANCOVA) will be used to measure whether total self-efficacy scores differ between the 2 groups, with adjustments for the pretest scores and any significant baseline characteristics.

For the first secondary objective, an ANCOVA will be used to determine whether scores differ between the 2 groups on social support, postpartum anxiety, and postpartum depression, with adjustments for the pretest scores and any significant baseline characteristics. For the second secondary objective, a 2-way ANCOVA will be used to measure whether the mean difference of self-efficacy scores differs between the 4 groups (multiparous/primiparous and intervention/control), with adjustments for any significant covariates on self-efficacy, social support, postpartum anxiety, and postpartum depression. For the third secondary objective, a 2-way repeated-measures ANCOVA will be used to explore whether changes in the key psychosocial outcome variables varied over time.

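### Secondary hypothesis 2 predicts no parity difference, but the plan gives it only a difference test at 0.05, which can reject equality and cannot support it

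*Protocol article*

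**What the plan says.** Four places in the protocol article bear on this.

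- **Effectiveness Hypotheses**, second secondary hypothesis: "there will be no difference based on parity on any of the psychosocial outcomes".
- **Effectiveness Objectives**, second secondary objective: "to determine whether the effect on any outcomes differs based on parity". This is a question about effect modification and is put neutrally.
- **Data Analysis**, for that objective: "a 2-way ANCOVA will be used to measure whether the mean difference of self-efficacy scores differs between the 4 groups". The four groups are parity crossed with arm. The sentence does not name the arm-by-parity term. It mentions adjustment for significant covariates but, unlike the sentences for the primary and first secondary objectives, does not mention the pretest score. The one criterion given is general: a P "value of 0.05 will be considered significant for all outcomes".
- **Sample Size**: it gives 30 women per cluster and 60 per arm, 120 in all, as the number that provides power for a parity-level analysis. The only effect size behind this is the feasibility study's baseline to 6-week change of 3.78 (SD 4.5). No size of parity difference to detect or to rule out is given.

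**The concern.** The hypothesis is a null put forward as the expected result. A difference test asks whether the data are incompatible with equality. When it does not reject, the reason may be that the effects are similar or that the estimate is imprecise, and the P value alone cannot separate the two. Under the plan as written, the only result that agrees with hypothesis 2 is P>0.05, and a smaller or noisier trial makes that result more likely.

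Parity is the stratification factor, the subject of a stated objective and part of the sample-size rationale, so the parity result will be read with interest. The risk is a report that the programme suits first-time and experienced mothers equally, when the data leave room for a benefit concentrated in one of the two groups.

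**Working it through.** **Inputs from the documents.** 30 women per parity-by-arm cell, 60 per arm, 120 in all; change 3.78, SD 4.5 (Sample Size). Significance level 0.05 (Data Analysis).

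**Assumptions.** Two-sided test; equal parity split; 120 women analysed; residual SD between 3.2 and 4.5. The documents attach 4.5 to a pre-post change, so it is roughly an upper bound once the pretest score is adjusted for. The lower end, 3.2, equals 4.5 × √(1 − 0.7²) and allows for a sizeable gain from covariates. The calculation covers the KPCS only, because no SD is given for the other three outcomes.

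**The plan's own figure.** For one comparison of two arms within one parity stratum, n per arm = 2 × [4.5 × (1.96 + 1.2816) / 3.78]² = 29.8, rounded up to 30. So 30 per cell comes out with two-sided 0.05 and 90% power if the stated intraclass correlation of 0.2 is left out. The power is not stated. With that correlation applied as a design effect of 1 + 29 × 0.2 = 6.8, 80% power would need 22.25 × 6.8 = 151.3, or 152 per arm, so the stated inputs do not by themselves fix the figure. On the reading that reproduces it, 30 per cell powers the arm comparison inside a parity stratum. It does not power the difference between strata.

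**Precision of the arm-by-parity difference.** It is a contrast of four cell means, so SE = SD × √(4/30).

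| Residual SD | SE | 95% CI half-width (t, 116 df) | Difference detectable with 80% power (2.80 × SE) |
|---|---|---|---|
| 4.5 | 1.64 | 3.25 | 4.6 |
| 3.9 | 1.42 | 2.8 | 4.0 |
| 3.2 | 1.17 | 2.3 | 3.3 |

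**How often a real difference would be non-significant** (noncentral t, 116 df):

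| True difference in effect between parity groups | SD 4.5 | SD 3.9 | SD 3.2 |
|---|---|---|---|
| 3.78 (that effect in one group, none in the other) | 37% | 25% | 11% |
| 1.89 (one group gets half the effect of the other) | 79% | 74% | 64% |

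Here 3.78 is borrowed as a benchmark for a between-arm effect. In the protocol it is a within-person change over time.

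**Sensitivity to parity mix.** If 40% of each arm were in one parity group, the SE at SD 4.5 becomes 4.5 × √(2/24 + 2/36) = 1.68. At 30% it is 4.5 × √(2/18 + 2/42) = 1.79. An uneven split loosens the interval somewhat but does not change the picture.

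**The case against.** The strongest reply is that nothing improper is stated. The objective is neutral, a difference test suits it, and the hypothesis may simply record what the investigators expect. The 0.05 sentence sets a general significance level and is not a decision rule for hypothesis 2. Interpretive detail may sit in a fuller plan that is not shown.

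Part of this stands. A reader might infer that the trial will declare equal effects whenever P exceeds 0.05. The documents do not say so, and the point should not be put that way. What remains is a mismatch between two things the article does state: a predicted null, and a test that cannot support one.

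A reader might also infer that the test could not detect even a difference as large as the whole 3.78-point planning figure. That depends on the SD. The difference detectable with 80% power is 4.6 at SD 4.5, but 2.80 × 3.5 × √(4/30) = 3.58 at SD 3.5, which is below 3.78. Across the range used here, a 3.78-point difference would be detected in 63% to 89% of trials. SDs above 4.5 would look worse, but the documents give no basis for them.

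Finally, the hypothesis wording alone could mean a parity main effect. The objective makes effect modification the likelier reading, and the logical difficulty is the same under either.

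**Conclusion.** The point holds as a mismatch between hypothesis and test. Hypothesis 2 cannot be supported by the analysis assigned to it, and the article states no other criterion that could support it.

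A non-significant parity result on the KPCS would still be compatible with true differences of roughly 2.3 to 3.25 points either side of the estimate. It would be a fairly common result (11% to 37%) if the effect were 3.78 points in one parity group and nil in the other, and the usual result (64% to 79%) if one group gained half as much as the other. These figures rest on 30 analysed per cell, an equal parity split, two-sided testing and a residual SD of 3.2 to 4.5.

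The issue is confined to a secondary objective, and the primary comparison is unaffected. It is a cheap improvement to the plan.

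**What to change.** 1. In Effectiveness Hypotheses, restate secondary hypothesis 2 as an estimation aim: the difference in programme effect between primiparous and multiparous women will be estimated for each psychosocial outcome.
2. In Data Analysis, name the arm-by-parity interaction term of the 2-way ANCOVA as the quantity of interest for each of the four outcomes, adjusted for that outcome's pretest score and reported with its 95% confidence interval.
3. Add that P>0.05 for this term will not be interpreted as equal effects, and that such a result will be reported as inconclusive over the range the interval covers.

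No equivalence margin is needed, since the aim becomes estimation and no claim of similarity is made.

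The cost is a change of wording in two sections, made while recruitment is under way and so to be recorded as an amendment. No extra participants or data are required. The sponsor gives up the option of declaring no difference by parity from a non-significant test.

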### Implementation Objective

The implementation objective is to evaluate the implementation extent (ie, enrollment rate and timing, withdrawal rate, number of messages received) and quality (ie, satisfaction, barriers, suggestions for improvement) of the Essential Coaching for Every Mother program.

## Methods

### Study Design

This study will be a 2-group, stratified, parallel-arm, hybrid type 1 effectiveness-implementation randomized controlled trial. Through the use of an effectiveness-implementation design, it is possible to evaluate intervention effectiveness while simultaneously evaluating real-world implementation to guide future development and revisions [25]. The intervention will be compared with standard care that is currently being provided across Nova Scotia, stratified by parity.

### Ethics Approval

The study has been approved by the IWK Health Research Ethics Board (#1024984) and the Nova Scotia Health Research Ethics Board (#1026534) and is registered with the clinicaltrials.gov Protocol Registration System (NCT04730570). The CONSORT-EHEALTH (Consolidated Standards of Reporting Trials of Electronic and Mobile HEalth Applications and onLine TeleHealth) checklist [26] will be followed to improve the reporting as an eHealth intervention trial. In reporting the process evaluation, the Template for Intervention Description and Replication (TIDieR) checklist and guideline will be used [27,28]. The TIDieR checklist offers a standardized way to describe the implementation and document any deviations that arise, which allows for not only replication but also clear reporting for comparison of interventions [27].

### Setting

This study is being conducted across Nova Scotia, Canada. In 2017, Nova Scotia had a total of 8197 live births [29]. Currently in Nova Scotia and across Canada broadly, there is no standardization of delivery of postpartum care within or between provinces [6]. Thus, there is a need for interventions targeting the postnatal period to enhance the postpartum experience for mothers in Nova Scotia.

### Inclusion Criteria

Participants will be recruited antenatally and postnatally. To enroll antenatally, participants must (1) be at least 37 weeks pregnant; (2) have daily access to a mobile phone with text messaging capabilities; (3) be ≥18 years of age; (4) live and give birth in Nova Scotia; and (5) speak and read English. To enroll postnatally, participants must (1) have an infant younger than 10 days of age; (2) have daily access to a mobile phone with text messaging capabilities; (3) be ≥18 years of age; (4) live and gave birth in Nova Scotia; and (5) speak and read English.

Participants will be excluded if (1) their newborn dies or is expected to die prior to leaving the hospital; (2) they have no access to a mobile phone, either personal or shared; (3) they are unwilling to receive text messages; (4) they decline to participate or withdraw; or (5) they previously participated in the development or feasibility phase of this project.

### Recruitment

A multipronged approach will be used to recruit women who are at least 37 weeks pregnant or within 10 days postpartum. All recruitment will occur remotely with no in-person promotion. The primary methods will be social media advertisements (eg, posting on relevant parent groups on Facebook, paid advertisements on Facebook) as well as study posters across the province (eg, on the Family Newborn Unit at IWK Health, in perinatal centers, in family medical offices, etc). Additional sources of outreach that may be used include promotion through public health, family resource centers, media outreach, posters in public places that pregnant and new parents frequent, and word of mouth.

While the text messages are one-way only, if a participant responds to a message with a question for clarification, the principal investigator or research team member may respond to provide clarification only. For example, if a participant asks if they will receive reminder messages, a brief message will be provided confirming that reminder messages will be sent. If there are requests for advice on their care or that of their baby, mothers will be referred back to their health care provider through a standardized message sent if a participant responds unexpectedly during the program.

### Screening and Baseline

Interested participants will contact the research team via text message to complete the automatic remote eligibility screening process. All participants will receive a welcome message as well as details about the study and what the study will entail. During the antenatal recruitment process, the woman’s phone number, first name, and due date will be collected via TextIt [30]. This information is required to ensure that follow-up messages are sent to the woman via her mobile device based on her due date.

During the antenatal screening process, participants will be screened for eligibility, and eligible participants will be informed of the need to send a text within 10 days after giving birth to be enrolled in the study. Women who have not yet given birth are sent messages at 39 weeks, 40 weeks, 41 weeks, and 42 weeks or until enrolled or withdrawn to remind them of the need to text the word “delivered” after giving birth. Participants who initiate contact before 37 weeks will be asked if they want to be sent follow-up messages once they reach 37 weeks until the sample size is reached.

Once a woman gives birth or enrolls after giving birth, she will be asked screening questions to ensure eligibility and determine parity for stratification. Additional details including the newborn’s name, preferred gender pronoun for the infant, infant’s date of birth, and parity will be collected at that time. Once stratified, participants will be randomized and informed of their group allocation. Participants who are randomized to the intervention group will be asked their preference on breastfeeding and formula feeding messages. All participants will be asked to complete the consent form and baseline survey. To remind participants to complete the survey, reminder text messages will be sent via TextIt every other day for 2 weeks (a maximum of 6 total messages) or until the survey is completed. An email will be sent as a final reminder to participants who have not yet completed the survey after day 14. If an email address was not provided, an expanded text message will be sent on day 14 instead. Participants will also be informed that they may message “STOP” to withdraw from the study at any time. If a participant withdraws from the study, they will not receive any further messages nor will they be asked to complete any future surveys. Participants who complete the baseline survey will receive an electronic gift card worth Can $15 (US $11.97).

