#### Intervention Group

Participants in the intervention group will receive the standard in-person care in the hospital in which they give birth. After enrollment into the study, participants will start receiving messages until 6 weeks postpartum. The messages will be sent automatically based on the age of the infant. Participants in the intervention group will receive Essential Coaching for Every Mother as early as the evening of the second day after giving birth. This could be as early as 17 hours after birth (if a woman delivered at 11:59 the night before) or as late as 41 hours (if a woman delivered at midnight). If a participant enrolls after the messages are designed to start, they will start the message flow based on when they gave birth. Messages are sent at 10 AM and 5 PM during the first 2 weeks and at 10 AM daily after that. This time was recommended by both women and health care providers during the development of the intervention [23].

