**Enrollment**									
	Eligibility screen	✓							
	Informed consent			✓		✓		✓	
	Randomization	✓							

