**Assessments**									
	Demographics			✓					
	Self-efficacy			✓		✓		✓	
	Social support			✓		✓		✓	
	Postpartum anxiety			✓		✓		✓	
	Postpartum depression			✓		✓		✓	
	Postpartum care and adjustment					✓		✓	
	Delivery experience					✓			
	Feeding experience					✓		✓	
	Health information seeking					✓			

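### Consent and the baseline survey follow randomisation and disclosure of the arm, so the pretest covariate in the ANCOVA can be affected by allocation and refusal of consent can differ by arm

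*Protocol article*

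**What the plan says.** The Screening and Baseline section describes the flow after birth. Eligibility and parity are checked, and then: "Once stratified, participants will be randomized and informed of their group allocation". Next comes a step for one arm only: "Participants who are randomized to the intervention group will be asked their preference on breastfeeding and formula feeding messages". After that: "All participants will be asked to complete the consent form and baseline survey". Survey reminders go out every other day for two weeks, with a final one at day 14. No closing date is given.

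Table 1 agrees. Randomisation is ticked under Enrollment. The "Informed consent" row is ticked at T1, T2 and T3 but not under Enrollment. The "Self-efficacy" row, like the rows for the other three scales, is first ticked at T1.

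On message timing, the Intervention Group section says: "After enrollment into the study, participants will start receiving messages until 6 weeks postpartum". Messages follow the infant's age, and a woman who enrols late joins the flow at that point.

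The Data Analysis section specifies ANCOVA for self-efficacy, and for the other three scales, "with adjustments for the pretest scores and any significant baseline characteristics". The Blinding section confirms that participants know their arm. All four scales are self-reported.

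**The concern.** ANCOVA on a pretest is safe when the pretest cannot depend on allocation. Here every pretest is given by a woman who has already been told her arm, and some may be given after messages have begun. If the programme has already raised the score, adjusting for it removes part of the effect the trial is meant to estimate. If knowing the arm changes how women rate themselves at baseline, through disappointment or expectation, the adjustment carries that shift into the 6-week comparison.

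There is also a question of who is analysed. Consent is requested after disclosure, and the exclusion list in the Inclusion Criteria section covers women who decline or withdraw. A woman can therefore decline because of her arm and leave the trial after randomisation. A woman with no pretest cannot enter the ANCOVA unless the missing score is handled in some way the article does not describe.

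**Working it through.** **Order of steps.** The Screening and Baseline text and Table 1 were compared with every other mention of baseline. The abstract equates baseline with enrolment after birth, and Study Measures sends the survey link upon enrolment. Neither puts consent or a pretest before randomisation.

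**Possible message exposure before the survey.** Counting the day of birth as day 1, the first message is on the evening of day 2. Days 3 to 14 carry two a day, and days 15 to 42 one a day: 1 + 12 × 2 + 28 = 53, which reproduces the stated total.
- Enrolled on day 2, survey 14 days later (day 16): 1 + 24 + 2 = 27 of 53 messages, about 51%.
- Enrolled about day 10, survey on day 24: 35 messages scheduled by then, less the 15 to 17 sent by days 9 to 10 before she joined, leaves 18 to 20 of 53.

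These are late responders. A woman who answers at once has had few or no messages, but she still knows her arm.

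**Effect on the estimate.** Let *b* be the slope of the 6-week score on the pretest and *d0* the between-arm shift already in the pretest. Then

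expected ANCOVA coefficient = true effect − *b* × *d0*.

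If *d0* is a share *f* of the true effect, the proportional loss is *b* × *f*, with *f* averaged over the women analysed. The document gives neither *b* nor *f*, so both are assumed. Taking the feasibility figure of 3.78 purely as a scale:

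| slope *b* | *f* = 25% | *f* = 50% |
|---|---|---|
| 0.2 | 3.59 (−5%) | 3.40 (−10%) |
| 0.5 | 3.31 (−12.5%) | 2.83 (−25%) |
| 0.7 | 3.12 (−17.5%) | 2.46 (−35%) |
| 0.88 | 2.95 (−22%) | 2.12 (−44%) |

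Worked cell: 3.78 × (1 − 0.5 × 0.25) = 3.31. Simulation with 60 per arm at slopes 0.5, 0.7 and 0.88 agreed to within about 0.02.

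**Power.** Assume SD 4.5 at both visits (so the slope equals the correlation *r*), two-sided 5% and 60 per arm. Then SE = 4.5 × √(1 − *r*²) × √(2/60) × √(1 + (*d0*/4.5)²/4).
- True effect 3.78: power stays at or above 0.97 in every cell of the table.
- True effect 1.89 (half), *r* = 0.5: power is 0.76 with a clean pretest, 0.64 at *f* = 25% and 0.51 at *f* = 50%.
- True effect 1.89, no pretest covariate: SE = 4.5 × √(2/60) = 0.82; 1.89/0.82 = 2.30; power = Φ(2.30 − 1.96) = 0.63.

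**Reporting shift only.** Suppose there is no 6-week effect, but knowing the arm moves baseline reports 1 point apart. The coefficient is then biased by *b* × 1 in the opposite direction to the shift. The type I error is about 0.06 at *r* = 0.2, 0.11 at *r* = 0.5 and 0.22 at *r* = 0.7, against 0.05. The sign depends on which arm reports higher.

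**The case against.** Several points on the other side are sound.

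- A reader might infer that messages definitely run for up to two weeks before baseline and that the pretest is contaminated. The document does not say so. Survey link and messages both follow enrolment and may nearly coincide. The text neither makes messages wait for the survey nor says they do not, and day 14 is the last reminder, not a deadline. Only the order of randomisation, disclosure, consent and survey is explicit.
- A reader might take the 44% cell as the likely loss. It combines the largest assumed share with 0.88, which is the test-retest reliability quoted for the scale and not a slope from baseline to 6 weeks. A share of messages is not a share of effect, and prompt responders pull the average down. The 3.78 is a pre-post change from the feasibility study, not a difference between arms.
- A reader might infer that the trial loses its power. It does not if the true effect is near 3.78. The loss matters only for a much smaller effect.
- Women receive study details before screening, so they are not uninformed when randomised. No refusal rate is given, so differential refusal is possible but not shown.

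None of this changes the order of steps or makes the pretest a pre-randomisation measure.

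**Conclusion.** The point holds for what the text and Table 1 state: consent and all four pretest scales come after randomisation and disclosure, and the ANCOVA adjusts for those scores. The scores can be affected by knowledge of the arm and, in late responders on the intervention, by early messages. Whether they are, and by how much, cannot be derived from the document. A loss of 12.5% (slope 0.5, average share 25%) is an illustration on assumed inputs. Early benefit in the pretest would bias towards no effect; a reporting shift could go either way, so the plan cannot be defended as merely conservative. Refusal that differs by arm is an additional route to bias, and removing the pretest covariate does not cure it. The order should be changed while recruitment continues, because it affects both what the primary analysis estimates and who enters it.

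**What to change.** **Women not yet randomised.** Obtain consent and completed KPCS, MSPSS, PSAS and EPDS before the TextIt random split, disclosure of the arm and the first message. Count the 140 at randomisation.

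**Women already randomised.** Report by arm the time from randomisation to baseline survey, the number declining consent and the number without a baseline. For the intervention arm, also report messages received before the survey. Give the 6-week comparison without the pretest covariate, keeping parity, alongside the ANCOVA. Do not restrict to surveys completed before the first message: control women have no such event, so the rule would select early responders in one arm only, and those surveys would still follow disclosure. Flagging surveys completed after disclosure does not help either, because on the stated order that is all of them.

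**Cost.** A change to the TextIt and REDCap flow and an ethics amendment. Some women will start messages later and miss early ones, because the flow follows infant age; on the count above, a woman who completes baseline on day 16 would miss up to 27 of 53. Women who do not complete baseline are not randomised. Women enrolled before and after the change have differently defined baselines and should be identified in the analysis. The comparison without the pretest is less precise than an ANCOVA on a clean pretest: at *r* = 0.5 its standard error is 1/√(1 − 0.25) = 1.15 times as large.
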